### Participant flow

The study design and participant flow are shown in Figure 2.

**Figure 2 F2:**
[figure not shown]
**Research design**.

#### Control group

Employees in the control group will receive the results of the physical test in writing with general information on physical activity and health. The results and information material is briefly explained to the employee. Their occupational health care is continued as usual.

#### Intervention group

After the physical testing employees assigned to the intervention group will receive their test results and information on physical activity. They will also receive a physical activity monitor (PAM, model AM 200, PAM BV, the Netherlands), which is an uni-axial accelerometer in the vertical direction that can be easily attached to a belt. The validity of the PAM accelerometer has been tested in a laboratory setting and has shown results similar to the MTI actigraph for estimating energy expenditure in walking and stair walking [27]. The PAM produces a single index score that accumulates during the day and is a proxy measure of total daily PA. The PAM shows the PAM score continuously on its display.

The participants have to install the PAM software on their computer in order to use the PAM reader. Via a USB cable, which must be connected to a computer with an internet connection, the user can upload his or her personal PAM scores through PAM software to the Aino Active (AA) website http://www.ainoactive.fi at any time throughout the day. When reading the PAM, the participant is automatically directed to the AA website. During the first visit, the user will register on the AA website by filling out a form with personal data (ie, username and password). Upon entry to the website, the user formulates a PAM goal score for the 12 month intervention period. Based on the first two weeks the employee and AA's coach can together decide to change the PAM goal. The PAM goal score can be changed by the user and AA's coach throughout the intervention. On every subsequent log-in, the AA's website presents all the uploaded PAM scores and coupled PAM goals in orderly graphs per week or month.

On the Aino Active website, users can interactively plan and evaluate their own activity advice based on their actual PAM scores and their PA goals and preferences. When an employee does not log on to the site every two weeks to download activity data she/he receives a phone call from the coach. The subjects in the intervention group will also participate in a physical test at 6 months of the intervention. Their occupational health care is continued as usual.

### Outcome measures, confounding- and mediating variables

Primary outcomes of the study are 1) physical activity level measured in MET hours per week, 2) health parameters (musculoskeletal and depressive symptoms) 3) work productivity and number of sickness absence days 4) healthcare utilisation. Effectiveness of the intervention is assessed by comparing the outcomes between the two treatment arms. Secondary outcomes are also listed in the Table 2.

**Table 2 T2:** Primary and Secondary outcome parameters

Outcome measure	Q, M, R	Baseline	6 months	12 months	24 months

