**Methods/Design:**

CoAct is a randomised controlled trial with two arms: a control group and intervention group with daily activity monitoring and distance counselling. The intervention focuses on lifestyle modification and takes 12 months. The study population consists of volunteers from 1100 eligible employees of a Finnish insurance company. The primary outcomes of this study are change in physical activity measured in MET minutes per week, work productivity and sickness absence, and healthcare utilisation. Secondary outcomes include various physiological measures. Cost-effectiveness analysis will also be performed. The outcomes will be measured by questionnaires at baseline, after 6, 12, and 24 months, and sickness absence will be obtained from the employer's registers.

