The physical activity monitoring and distance counselling concept combines the use of a personal activity monitor with web-based tailored physical activity advice. Users can interactively plan and evaluate their own activity advice based on their actual PA scores and their PA preferences and goals. A recent randomised controlled trial [21] evaluated the effectiveness of such online physical activity advice based on a personal activity monitor and found that a 3-month intervention did not significantly affect PA levels and, furthermore, that a higher adherence to the program did not result in increased levels of PA. The study group comprised of a total of 102 physically inactive employees, 23 to 39 years old.

The main purpose of the present study is to evaluate the effectiveness on physical activity of a lifestyle programme with daily monitoring of activity and distance counselling compared to self help instruction, in a large cohort with a broad age spectrum of employees, at 12 months. Employees in the intervention group are given accelometers to wear daily and they will receive counselling via telephone and secure web messages. Subsequent purposes are to determine effects of the distance counselling on work productivity, sickness absence, healthcare utilisation and health outcomes when comparing to self help.

In the study we will be analyzing the lifestyle intervention's influence to health behaviour and if changes in health behaviour affect overall health. We are also interested in the lifestyle program's effects on productivity at work, including the potential effects on sickness absence. Furthermore, we will analyse potential effect modifying and mediating factors.

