**PRIMARY OUTCOMES**					
PHYSICAL ACTIVITY					
Physical Activity	Q	v	v	v	v
HEALTH RELATED					
Musculoskeletal disorders	Q	v		v	v
Depression score	Q	v		v	v
Healthcare service utilization	Q and R	v	v	v	v
PRODUCTIVITY PARAMETERS					
Sickness absence	R				
Work productivity	Q	v	v	v	v

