### Primary outcome measurements

#### Physical activity

The volume (frequency, intensity, duration) of leisure time and way to work physical activity are assessed by a self-administered questionnaire based on International Physical Activity Questionnaire (IPAQ). Total MET (metabolic equivalent) score MET min-per-week (continuous score from the IPAQ scoring protocol) is calculated as follows: (daily minutes of walking × days per week with walking × 3,3) + (daily minutes of moderate-intensity activity × days per week with moderate intensity activity × 4,0) + (daily minutes of vigorous activity × days per week with vigorous activity *8,0)[28] The MET values are derived from the IPAQ validity and reliability study [29]. In addition we will calculate truncated MET-minutes per week, in which all daily minutes exceeding 120 min will be truncated to 120 min. This rule has been proposed in the "Guidelines of Data Processing and Analysis of IPAQ Short Version" with the attempt to normalize skewed population data.

All participants will receive the physical activity questions as part of the questionnaire sent to them at the beginning of this study, as well as at 6 and 12 months from the intervention.

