### Sample size

The standard deviation for the IPAQ score in our population was estimated to be 1500 MET min-per-week. A difference of 400 MET min-per-week between treatment arms will be detectable with 85% power in two-tailed tests with the alpha of 0.05 for a sample of 253 employees in each group; the standardized effect size will be 0.25.

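### The protocol gives two different lists of primary outcomes, four in the abstract and six in the methods, while its alpha and sample size serve physical activity alone

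*Protocol article*

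**What the plan says.** The protocol article states its primary outcomes in three places, and they do not agree.

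- Abstract, Methods/Design: "The primary outcomes of this study are change in physical activity measured in MET minutes per week, work productivity and sickness absence, and healthcare utilisation". That is four measures.
- Outcome measures, confounding- and mediating variables (methods text): four numbered groups holding six measures. The sentence opens "Primary outcomes of the study are 1) physical activity level measured in MET hours per week, 2) health parameters (musculoskeletal and depressive symptoms" and its last two groups read "3) work productivity and number of sickness absence days 4) healthcare utilisation".
- Table 2, primary block: six rows, including "Musculoskeletal disorders" and the depression score.

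The detailed descriptions under Primary outcome measurements cover activity, productivity, sickness absence and healthcare utilisation, so they follow the abstract's list and not Table 2.

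Two other sections single out activity. The Background says "The main purpose of the present study is to evaluate the effectiveness on physical activity of a lifestyle programme", fixes this at 12 months, and ranks productivity, absence, healthcare use and health outcomes as subsequent purposes. The Sample size section says "A difference of 400 MET min-per-week between treatment arms will be detectable with 85% power in two-tailed tests with the alpha of 0.05", and gives no calculation for any other outcome.

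The activity measure also varies. The abstract, the Physical activity subsection and the Sample size section use MET minutes per week, while the outcome section uses MET hours. The Physical activity subsection defines a total score by formula and then adds a second version: "In addition we will calculate truncated MET-minutes per week, in which all daily minutes exceeding 120 min will be truncated to 120 min".

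**The concern.** The outcome labelled primary decides whether a trial is reported as positive. Under the abstract, a result on depressive symptoms is not primary; under the outcome section and Table 2 it is. Under the Background and the Sample size section, neither it nor productivity nor sickness absence should carry the main conclusion. An analysis plan takes its primary outcome from the protocol, and here it would receive conflicting answers.

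Two things are at stake. If several outcomes really are co-primary and any one could establish success, the type I error is no longer the 5% in the Sample size section. If that error were instead controlled by splitting alpha, activity would lose the power the trial was sized for. The Discussion sharpens this: it speaks of sufficient power for activity and also for subsequent health and productivity, although only activity was sized.

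**Working it through.** **1. The plan's own figure.** Inputs from the Sample size section: difference 400, SD 1500 MET-min per week, two-sided alpha 0.05, power 85%, equal groups.

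n per group = 2 × (z₀.₉₇₅ + z₀.₈₅)² × (SD/difference)² = 2 × (1.960 + 1.036)² × (1500/400)² ≈ 252.5, rounded up to 253.

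The plan's 253 reproduces. Power at 253 is 85.1% by the normal formula and 84.9% by the t test. The whole 0.05 goes to this one comparison.

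**2. Counting the primary outcomes.**

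| Measure | Abstract | Outcome section and Table 2 | Sized |
|---|---|---|---|
| Physical activity | yes | yes | yes |
| Work productivity | yes | yes | no |
| Sickness absence | yes | yes | no |
| Healthcare utilisation | yes | yes | no |
| Musculoskeletal symptoms | no | yes | no |
| Depressive symptoms | no | yes | no |
| Total | 4 | 6 | 1 |

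**3. Family-wise error if any one significant primary outcome counted as success.** This rule is an assumption; the protocol does not state it. With k independent tests at 0.05 the error is 1 − 0.95^k:

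- k = 4: 1 − 0.95⁴ = 18.5%
- k = 6: 1 − 0.95⁶ = 26.5%

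The protocol gives no correlations, so a common correlation ρ between the test statistics is assumed. With c = 1.96, the error is 1 − ∫ [Φ((c − √ρ x)/√(1 − ρ)) − Φ((−c − √ρ x)/√(1 − ρ))]^k φ(x) dx:

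| ρ (assumed) | 4 outcomes | 6 outcomes |
|---|---|---|
| 0 | 18.5% | 26.5% |
| 0.3 | 17.4% | 24.1% |
| 0.5 | 15.6% | 20.7% |
| 0.7 | 13.0% | 16.4% |

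**4. The price of splitting alpha instead (Bonferroni, activity included).**

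- Four outcomes, alpha 0.05/4 = 0.0125: power for activity at 253 per group is 69.2%; 352 per group would restore 85%.
- Six outcomes, alpha 0.05/6 = 0.0083: power is 64.1%; 380 per group would restore 85%.
- Activity as sole primary outcome: alpha 0.05 and 253 per group, unchanged.

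**5. The unit.** 400 MET-min is 400/60 = 6.7 MET-h. This is a linear rescaling: it changes how a result reads, but no test or p-value.

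**The case against.** The strongest reply is that the protocol does rank its outcomes. The Background gives activity at 12 months as the main purpose and the rest as subsequent, and the sample size follows that ranking. This stands as evidence of intent, and the fix relies on it. It does not remove the conflict, because the abstract, the outcome section and Table 2 still apply the word primary to the other measures, and they disagree on which.

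It can also be said that only a condensed article is at hand and that a multiplicity procedure may sit in an analysis plan not shown. That stands too: the absence of such a procedure is not the finding. The contradiction is in the printed text, and an unseen plan does not resolve it.

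Several stronger readings are tempting but unsupported:

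- A reader might infer that a false positive primary result will occur about one time in four. That needs the six-outcome list, near-independent tests and an any-one-wins rule. The Statistical analyses section promises only group summaries, effect sizes and confidence intervals for each outcome.
- A reader might count every outcome-by-visit cell in Table 2 as a primary test: 3 + 2 + 2 + 3 + 3 + 1 = 14 cells, giving 1 − 0.95¹⁴ = 51%. Repeated measures on the same people are not independent, no section makes each visit a primary test, and the Background points to 12 months. This figure should not be used.
- A reader might treat change versus level of activity as two different outcomes. With randomised arms and a baseline measurement, both target the same between-arm difference and differ only in precision.

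**Conclusion.** The point holds as an internal contradiction: four primary outcomes in one place, six in two others, and a design sized at two-sided 0.05 for one of them. The wrong unit in the outcome section is a slip that should be corrected alongside it.

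The size is conditional. Only if any single unadjusted significant primary outcome were taken as success would the family-wise error be 18.5% to 26.5% under independence, or about 16% to 21% at an assumed correlation of 0.5. Those figures show what the ambiguity would permit; they do not describe an error rate the protocol commits to. The contradiction itself rests on no assumption and should be resolved before results are analysed, since the main conclusion depends on which list is used.

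**What to change.** In the abstract, the outcome section and Table 2, name IPAQ total MET-minutes per week at 12 months as the single primary outcome, and label the other five outcomes secondary. This follows the stated main purpose and the sample size, and leaves alpha at 0.05 and the target at 253 per group.

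In the same revision:

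- Correct MET hours to MET minutes in the outcome section.
- State that the total score from the formula in the Physical activity subsection is primary and the truncated score a sensitivity analysis. That subsection introduces truncation as an extra calculation. The Sample size section says only IPAQ score, so the sponsor should confirm that the SD of 1500 refers to the total score.
- Describe the other time points as supportive.
- If confirmatory claims on the other outcomes are wanted, test them only after activity is significant, in a fixed order or with Holm among themselves. Putting activity inside the Holm set would expose it to the power loss shown above.

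The cost is wording, plus the sponsor giving up the primary label on productivity, absence, healthcare utilisation and the two symptom outcomes. All of them can still be reported with effect sizes and confidence intervals as planned.

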**PRIMARY OUTCOMES**					
PHYSICAL ACTIVITY					
Physical Activity	Q	v	v	v	v
HEALTH RELATED					
Musculoskeletal disorders	Q	v		v	v
Depression score	Q	v		v	v
Healthcare service utilization	Q and R	v	v	v	v
PRODUCTIVITY PARAMETERS					
Sickness absence	R				
Work productivity	Q	v	v	v	v
**SECONDARY OUTCOMES**					
Body weight	M	v	v	v	
Body height	M	v			
Waist circumference	M	v	v	v	
Body fat percentage	M	v	v	v	
Blood pressure	M	v	v	v	
Aerobic fitness; VO2 Max	M	v	v	v	
Programme costs	R				

Q = Questionnaire, M = Measurement, R = Registry

Assessment of the secondary outcomes is done either by questionnaire, measurements during the physical test, or by collecting data from occupational healthcare provider and employer's absenteeism/payment records.

### Primary outcome measurements

#### Physical activity

The volume (frequency, intensity, duration) of leisure time and way to work physical activity are assessed by a self-administered questionnaire based on International Physical Activity Questionnaire (IPAQ). Total MET (metabolic equivalent) score MET min-per-week (continuous score from the IPAQ scoring protocol) is calculated as follows: (daily minutes of walking × days per week with walking × 3,3) + (daily minutes of moderate-intensity activity × days per week with moderate intensity activity × 4,0) + (daily minutes of vigorous activity × days per week with vigorous activity *8,0)[28] The MET values are derived from the IPAQ validity and reliability study [29]. In addition we will calculate truncated MET-minutes per week, in which all daily minutes exceeding 120 min will be truncated to 120 min. This rule has been proposed in the "Guidelines of Data Processing and Analysis of IPAQ Short Version" with the attempt to normalize skewed population data.

All participants will receive the physical activity questions as part of the questionnaire sent to them at the beginning of this study, as well as at 6 and 12 months from the intervention.

#### Work productivity

Work productivity is measured with the QQ instrument [30]. Respondents will be asked to indicate how much work they actually performed during regular hours on their last regular workday as compared with normal. The quantity of productivity is measured on 10-point numerical rating scale; 0 representing "nothing" and 10 representing "normal quantity" [30,31]. The self-reported productivity of the QQ instrument has been shown to correlate with the objective work output [31]. The questionnaire is sent to each employee at baseline, 6 and 12 months.

#### Sickness absence

Sickness absence days are analyzed from company's absenteeism and payroll records - each employee is required to inform the company when sick for one day to three days and required to get a certificate from occupational health when sick for longer than three days. Sickness absence data will also be collected for each employee from the year preceding the intervention in order to compare change over time.

#### Healthcare utilization

As part of the first questionnaire the employees will be requested to complete a questionnaire concerning healthcare resource use during the past 6 months. This questionnaire includes questions of different healthcare resources used. This questionnaire is presented again at the 6 and 12 month time points.

Healthcare utilization data is also retrieved from occupational healthcare records. Data is retrieved based on social security number and study period data is compared to data from preceding year on individual level.

### Secondary outcome measures

Secondary outcome measures are listed in Table 2 and are presented here in more detail.

#### Body Weight and body height

Body weight is measured in kg, to the nearest 0,1 kg with a digital scale (BC-418, MA). Participants are wearing light clothing and no shoes. Body height is measured in m, to the nearest 0.001 m with a portable meter (Charter HM 200P). Positioning of the body is standardized by asking the subject to stand straight, without shoes and heels together. Both weight and height are measured twice and for each mean value of the two measurements is computed.

#### BMI

BMI is calculated by dividing the measured body weight (kg) by the squared measured body height (m).

#### Waist circumference

Waist circumference (in cm) is measured twice with a measuring tape (Reiju Oy) with a range of 0-150 cm. Waist circumference is measured to the nearest 0,5 cm, at the midpoint between lower border of the ribs and the upper border of the pelvis. A means value of the two measurements is computed.

#### Body fat percentage

Body fat percentage is measured with a body fat analyzer device (TANITA) [32].

#### Blood pressure

Blood pressure is measured with a fully automated blood pressure monitor (Omron M3 Intellisense). A regular size cuff is used on the right upper arm. The right arm is placed on a table so as the cuff is on a level with the heart. After the employee has rested for 5 min in a sitting position, blood pressure is measured twice. A mean value of the two measurements is computed. Employees that have a blood pressure of 140/90 mmHg or higher are advised to visit their occupational healthcare provider.

#### Aerobic fitness

Aerobic fitness is measured by means of the estimated VO2 max during the indirect bicycle ergometer test.

### Sample size

The standard deviation for the IPAQ score in our population was estimated to be 1500 MET min-per-week. A difference of 400 MET min-per-week between treatment arms will be detectable with 85% power in two-tailed tests with the alpha of 0.05 for a sample of 253 employees in each group; the standardized effect size will be 0.25.

### Statistical analyses

The effect of the intervention will be estimated on an individual level based on the intention-to-treat principle. For each primary and secondary outcome, a summary of results for each group, and the estimated effect size and its precision with confidence intervals will be presented. We will also assess potential effect modifying and mediating factors. The potential modifiers and mediators have been predefined and will all be measured at baseline. The potential effect modifiers are personal characteristics (age and gender), the result of the health risk appraisal (high/intermediate/low risk), baseline self-rated level of physical activity, baseline level of the ergometer test; job characteristics (specialist/manager), sick-leave related characteristics (sick leave days in the past year), and self-rated disability thoughts. The potential effect mediating factors are attendance to the PA intervention as intended, healthcare utilisation, and sick-leave related characteristics (sick leave days during the follow-up year).

#### Cost-effectiveness analysis

Cost-effectiveness analyses (CEA) will be conducted from the societal perspective and cost-benefit analyses (CBA) from the employer perspective. To estimate cost and effect differences, relating confidence intervals and cost-effectiveness ratios bootstrapping techniques will be used. Cost-effectiveness planes and acceptability curves will be presented. Additionally, subgroup analyses will be performed. The cost of intervention includes costs that are directly related to the implementation of the program. Besides the cost of intervention itself, direct health care costs will be included. Also indirect costs resulting from a loss of production due to absenteeism from paid work will be analysed.

## Discussion

Decreased productivity at work is an important consequence of the presence of health problems. On the other hand numerous health problems can be prevented and treated with the right amount of daily physical activity. CoAct is motivated by the increasing interest in prevention in occupational health. The research presented here analyzes a lifestyle intervention's effects to health behaviour (changes in physical activity). Further on we will look at health behaviour effects on overall health, absenteeism and efficiency at work. The employee is considered a core part of preventive healthcare services as he or she can be in an important role as value cocreator, and contribute input to the healthcare process, such as enhanced levels of (daily) physical activity to avoid chronic conditions and to improve overall healthcare outcomes.

Some limitations of this study can be mentioned. Neither the self-administered questionnaires nor the accelometers are the perfect gold standard measure of physical activity [33-35]. Accelometers alone cannot provide contextual information about the type or purpose of specific activities. Also, due to the study design we can only track the change in physical activity for the whole population by the means of questionnaire that may be rather insensitive as an outcome measure.

Studying the effects of this intervention is important, as it contributes to our understanding on the effectiveness of this novel method of lifestyle intervention, physical activity monitoring with distance counselling. The intervention has in Finland been taken into clinical use, but randomised trials of the effectiveness of the method are yet almost lacking. This type of intervention has not been evaluated in this specific setting with such a significant population yet. We designed our study as pragmatic as possible for the purpose of studying the role of PA monitoring and distance counselling in the co-creation of value, namely physical activity. If proven effective the employee will benefit from an improved lifestyle and a reduced risk of illness, while the employer will benefit from healthier, more productive workers and lower absenteeism. If proven cost-effective, this type of intervention may be implemented on a larger scale in the future. If proven not effective despite sufficient power to detect a clinically meaningful change in activity level, and subsequent health and productivity at work, the finding will help in allocating occupational health resources to be used otherwise.

## APPENDIX 1

Exclusion criteria - physical testing

